### Primary outcomes

The primary outcome for randomisation 1 (ATT regimen comparison) is all-cause mortality at 48 weeks. The primary outcome for randomisation 2 (aspirin/placebo comparison) is the modified Rankin Scale (mRS), dichotomised as death (score 6 out of 6) or severe impairment (score 5) versus the rest (score 0–4) at 48 weeks.

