### Screening procedures

Parents/carers of children with presumptive TBM are invited to participate after the child is identified as potentially eligible. Informed consent is obtained from parents/guardians prior to trial participation, with assent additionally sought from children who are developmentally and cognitively capable, as per local ethics committee guidance. The consent information is provided in the local language using locally translated patient information sheets and consent forms (online supplemental material). Different treatments and possible toxicities by arm will be explained before performing trial-specific procedures or any blood is taken for the trial. If a child is too unwell (eg, comatose) to provide assent, parent/guardian consent is sufficient, and assent, if developmentally appropriate, is taken at a later date when the child’s condition improves. Participants undergo a screening assessment, including TB symptoms and risk factors, and a physical examination, including anthropometric evaluations, seizure frequency, Glasgow coma scale, focal neurology and TBM severity (Medical Research Council grade) (online supplemental table S1a). CSF is collected (unless already collected <7 days prior to screening) by lumbar puncture or ventricular shunt for microscopy, biochemistry and TB diagnostics, that is, acid fast stain, Xpert MTB/RIF (Mycobacterium tuberculosis/rifampicin), Xpert Ultra or Truenat (whichever is available) and mycobacterial culture. Safe CSF volumes are collected according to published guidance.^44^ Cultured isolates are sent for drug susceptibility testing (DST) of *Mycobacterium tuberculosis*, in addition to resistance (if any) already identified on nucleic acid amplification testing. A gastric aspirate or alternative respiratory sample are collected prior to commencing ATT or within 7 days of commencement.

TBM diagnostic certainty is determined retrospectively based on the established uniform case definition for TBM.^45^ For children living with HIV and CD4 counts of <100 cells/mL, India Ink or cryptococcal antigen testing is performed. Phenotypic DST is done on positive cultures in real time. Repeat TB diagnostics are completed at the time of suspected TB treatment failure or relapse/recurrence. Cultures positive for *M. tuberculosis* are stored for strain genotyping. Participants have a chest X-ray and neuroimaging of the brain at enrolment or as soon as clinically feasible.

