### Statistical considerations

#### Sample size

The study is powered by the comparison of the shortened ATT versus standard control ATT, as this requires a larger number of patients. Based on a non-inferiority margin of 10%, 394 (rounded to 400) children would be needed to demonstrate non-inferiority, with 90% power, 2-sided 5% alpha and 5% loss to follow-up at 1 year, assuming 20% mortality in the control regimen and 17% (ie, a 3% (absolute) improvement) in the intensified shorter regimen. Control arm estimates are based on a recent meta-analysis,^3^ and the assumption of a 3% improvement in the intervention arm is based on the reported lower mortality with the intensified short regimen used in Cape Town.^15^

Assuming 50% of children in the placebo arm die or suffer severe impairment,^3^ 400 children would provide approximately 90% power, 2-sided 5% alpha, to detect a difference of at least 16% (superiority margin) in the aspirin arm when compared with placebo. The largest TBM aspirin trial to date reported 45% and 50% reductions in stroke and mortality, respectively.^41^ Following regular consultations with the independent data monitoring committee (IDMC) and trial steering committee (TSC), if the planned recruitment of 400 children is not possible, the modified target of 300 children would be acceptable to allow 80% power and 350 children to allow 85% power.

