#### Primary analysis

Primary outcomes for *randomisation 1* is mortality from all causes at 48 weeks. The primary analysis is based on the difference in proportion of deaths between the two arms at 48 weeks. The difference will be adjusted for minimisation factors using Cochran-Mantel-Haenszel weights. Alternative methods will be considered should sparse data within strata lead to unstable estimation.

Non-inferiority will be assessed using the upper bound of the two-sided 95% CI for this absolute difference. If the upper bound of this CI is less than 10% (the margin of non-inferiority), the intervention arm is considered to be non-inferior to the control arm.

*Randomisation 2* is designed to test for superiority of the aspirin versus placebo. mRS outcomes will be dichotomised as death (score 6) or severe impairment (score 5) versus the rest (score 0–4) and will be analysed using logistic regression adjusting for the minimisation factors.

As a secondary analysis, mRS will also be analysed using four groups: death or severe impairment (scores 5–6), moderate disability (scores 3–4), mild disability (scores 1–2) and full recovery (score 0).

This factorial trial assumes no statistical interaction between the two randomisations. An mITT analysis will be considered primary, and any exclusion from a full ITT analysis is detailed and justified in the SAP.

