#### Planned subgroup analysis

All subgroup analyses described here are exploratory. Subgroup analyses will be carried out and analysed for the primary efficacy endpoint for the mITT population. Subgroup analyses defined below will be performed for the mITT primary analysis for each randomisation 1 and 2 (Box 3).

Box 3Planned Subgroup analysesRegion* (Africa, India and Vietnam).Age group* (<2 years and ≥2 years).Sex (male and female).TBM stage using BMRC (1 and 2 combined, 3)*.ATT treatment prior to randomisation (< 7 days; ≥ 7 days)HIV status*.TBM baseline categorisation (definite and probable combined, possible).*Denotes minimisation factor. ATT, antituberculosis therapy; BMRC, British Medical Research Council and TBM, tuberculous meningitis.

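### Adjusting the primary mortality difference only for the minimisation factors, by CMH weights, gives away a little precision that severity data already collected could recover

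*Protocol article*

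**What the plan says.** All references are to the protocol article.

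- **Endpoint and rule.** Primary outcomes: "The primary outcome for randomisation 1 (ATT regimen comparison) is all-cause mortality at 48 weeks". Under Primary analysis, the short regimen is non-inferior if the upper limit of the two-sided 95% CI for the absolute difference lies below 10 points.
- **Adjustment.** Primary analysis: "The difference will be adjusted for minimisation factors using Cochran-Mantel-Haenszel weights". The next sentence is the fallback: "Alternative methods will be considered should sparse data within strata lead to unstable estimation". Neither a trigger nor a replacement method is named in the article.
- **Factors.** Box 3 (Planned subgroup analysis) marks minimisation factors with an asterisk: region (three levels), age group (two), HIV status, and stage. Stage is listed as "TBM stage using BMRC (1 and 2 combined, 3", then a closing bracket and the asterisk.
- **Data collected.** Screening procedures lists, among the baseline assessments, "seizure frequency, Glasgow coma scale, focal neurology and TBM severity (Medical Research Council grade". No adjustment for GCS or for stage 1 versus stage 2 is stated.
- **Sample size.** "Based on a non-inferiority margin of 10%, 394 (rounded to 400) children would be needed to demonstrate non-inferiority". The inputs given there are mortality of 20% on control and 17% on the short regimen, power of 90%, a two-sided 5% level, and 5% lost by one year. The same section accepts 350 children for 85% power and 300 for 80%. Study status reports that recruitment ended at 369.

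**The concern.** Two features of the stated estimator could cost precision.

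First, a CMH-weighted difference over fully crossed factors compares arms only within cells. A cell holding children from one arm has zero weight, so its children and deaths leave the estimate. Cells with unequal arms are used inefficiently. With many cells and a few hundred children, both will happen.

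Second, the adjustment set stops at the minimisation factors. Coma score and severity grade are plausible predictors of death and are recorded before treatment can affect them. Leaving out GCS and merging stages 1 and 2 forgoes variance reduction that needs no new data.

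At stake is the width of one confidence interval judged against one margin. Neither feature biases the comparison in any important way. The question is whether the same children could give a tighter interval at little cost.

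**Working it through.** **1. The plan's own figure.** Inputs from Sample size: 20% v 17% mortality, margin 10 points, two-sided 5%, 90% power, 5% loss.

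n per arm = (1.960 + 1.2816)² × (0.20×0.80 + 0.17×0.83) / (0.10 + 0.03)² = 10.507 × 0.3011 / 0.0169 = 187.2

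Total = 2 × 187.2 / 0.95 = 394.1, against the stated 394. The same formula gives power of 80.7% at 300, 86.3% at 350 and 90.4% at 400, in line with the stated 80%, 85% and 90%. At 369 it gives 88.0%. None of these takes credit for covariate adjustment.

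**2. Number of cells.** 3 × 2 × 2 × 2 = 24 if region, age, stage and HIV (taken as two levels) are fully crossed. That is 369/24 = 15.4 children per cell. Expected deaths are 0.185 × 369 × 0.95 ≈ 65, or 2.7 per cell. With stage in three levels there would be 36 cells and no ignored stage split.

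**3. What CMH does with them.** The weight of cell k is w = n₁n₀/(n₁ + n₀), which is zero if either arm is empty. With N children split evenly in every cell the weights sum to N/4.

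This was simulated with 6,000 trials per scenario and 351 analysed of 369 (about 5% loss). Allocation was by minimisation on the four factors with a biased coin of 0.8. The documents give none of the following, so they are assumptions:

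- stage 1/2/3 mix 25/45/30%; region mix 30/25/45%; 40% under 2 years
- HIV 30% in Africa and 2% elsewhere
- log odds ratios for death of 0.7 (HIV) and 0.4 (age)
- a GCS-like severity score with odds ratio 1.65, 2.7 or 4.5 per SD

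Result: about 19 cells occupied, about 16 with both arms, about 4 children dropped. The weights sum to 0.960 of N/4, that is 84.2 of 87.75. The largest CMH bias was 0.2 points.

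**4. Power at a true 20% v 17%, with 351 analysed.**

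| Severity effect (OR per SD) | CMH, 24 cells | Standardised, same factors | + three-level stage | + GCS | Unadjusted |
|---|---|---|---|---|---|
| 1.65 | 88.7% | 89.6% | 89.8% | 90.0% | 88.9% |
| 2.7 | 90.9% | 91.3% | 91.9% | 92.6% | 89.7% |
| 4.5 | 92.7% | 93.5% | 94.0% | 95.3% | 90.4% |

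Using unrounded results, the total gain over CMH is 1.2, 1.7 and 2.6 points. Changing the estimator on the same factors gives 0.4 to 0.9 of this; stage and GCS add 0.3 to 1.8.

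**5. Variance.** Empirical variance relative to the unadjusted difference, full model against CMH: 0.987/1.038 = 0.951, 0.970/1.017 = 0.954 and 0.918/1.017 = 0.903, so 5% to 10% lower. A separate repeat over the same range of severity effects gave 4% to 10%.

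As a check, put a variance reduction r into the formula of step 1 at 369: power = Φ(0.13/(0.04145 × √(1 − r)) − 1.96). This gives 88.0% at r = 0, 89.3% at r = 0.04 and 91.1% at r = 0.10, a gain of about 1 to 3 points.

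**6. Interval width.** From the mean standard errors, the CI half-width falls from 1.96 × 0.0411 = 8.06 to 1.96 × 0.0402 = 7.88 points (weak effect), from 7.78 to 7.51 (moderate) and from 7.45 to 7.02 (strong). The upper limit moves by about 0.2 to 0.4 points.

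**7. Type I error.** At a true difference of +10 points (moderate and strong effects), non-inferiority was declared in 2.7% to 2.8% of trials with CMH, about 2.5% with standardisation on the same factors, and about 2.7% with stage and GCS added. The simulation error is √(0.025 × 0.975/6000) ≈ 0.2 points, so these do not separate the methods.

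**The case against.** The plan is conventional. It names the effect measure, the adjustment set, the weighting and the decision rule, and adjusting for the allocation factors is normal practice. Changing the estimator on the same factors gains less than one power point. The rest comes from assumed prevalences and an assumed severity effect acting directly through the score, which favours the proposal; a real coma score over ages 29 days to under 18 years may predict less well. Full crossing and two-level stage coding are inferred from a subgroup list. Replacing a published estimator after recruitment closed, in an open-label comparison, is not free either. All of this stands, and it is why the point is minor.

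Four stronger readings are tempting and are not supported:

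- **CMH is unstable here.** Sparse cells occur, but bias is at most 0.2 points and 96% of the ideal weight is kept. With moderate or strong severity effects, CMH has more power than the unadjusted analysis that the sample size assumes (90.9% v 89.7%; 92.7% v 90.4%). With a weak effect it is level (88.7% v 88.9%).
- **The trial is underpowered because it stopped at 369.** The plan accepts 350, and its own formula gives 88.0% at 369.
- **The unnamed fallback is itself a defect.** A trigger and replacement method are what an article commonly leaves to the SAP. Primary analysis refers to a SAP, which is not shown and may settle this.
- **Randomisation 2 loses power in the same way.** No calculation here supports a figure for it, and no fault in its logistic model is shown.

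**Conclusion.** The point holds as a minor improvement to efficiency. As stated, the primary estimate uses only the minimisation factors. Crossed into up to 24 cells, it would drop about 4 children and leave baseline GCS and the stage 1 versus 2 distinction unused. The cost is about 4% to 10% of variance, 1 to 3 power points, or 0.2 to 0.4 points on the upper confidence limit.

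These sizes depend on two readings of the text (full crossing, two-level stage) and on prevalences and severity effects that the documents do not give. CMH remains a valid analysis, and no stated sample size or power is wrong.

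**What to change.** Before any analysis by arm, make the randomisation 1 primary estimate the standardised risk difference from a logistic model. Use main effects for arm, region, age group, HIV status, BMRC stage in three levels and baseline GCS, with a robust or delta-method 95% CI compared with 10 points. Prespecify the age-appropriate version of the coma score and its coding: Screening procedures names the Glasgow scale, while Study follow-up uses the Blantyre score for recovery from coma.

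Keep the CMH estimate as a sensitivity analysis. Every analysed child then contributes, all minimisation factors stay in the model, and the open fallback sentence can go. The same covariates may be added to the randomisation 2 model.

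The cost is SAP wording and minor programming; the covariates are already collected at screening. The real downside is a change to a published primary estimator after recruitment closed. Date and document it as made without sight of outcomes by arm, and keep the delegated statistician who has access to allocations out of the decision.

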#### Planned subgroup analysis

All subgroup analyses described here are exploratory. Subgroup analyses will be carried out and analysed for the primary efficacy endpoint for the mITT population. Subgroup analyses defined below will be performed for the mITT primary analysis for each randomisation 1 and 2 (Box 3).

Box 3Planned Subgroup analysesRegion* (Africa, India and Vietnam).Age group* (<2 years and ≥2 years).Sex (male and female).TBM stage using BMRC (1 and 2 combined, 3)*.ATT treatment prior to randomisation (< 7 days; ≥ 7 days)HIV status*.TBM baseline categorisation (definite and probable combined, possible).*Denotes minimisation factor. ATT, antituberculosis therapy; BMRC, British Medical Research Council and TBM, tuberculous meningitis.

## Ethics and dissemination

Ethics approval was received from the University College London (UCL) research ethics committee, London, UK (14935/0010); the institutional ethics committee, Postgraduate Institute of Medical Education and Research, Chandigarh, India (IEC-04/2019–1171); the ethics committee for human research, Lady Hardinge Medical College, Delhi, India; the University of Zambia Biomedical Research ethics committee, Zambia (0050419); joint research ethics committee University of Zimbabwe, Zimbabwe (83/19); the Mulago Hospital research and ethics committee; the ethics research committee Pham Ngoc Thach Hospital, Ho Chi Minh City, Vietnam; the ethics research committee Children’s Hospital 2, Ho Chi Minh City, Vietnam; the ethics research committee National Lung and TB Hospital, Ha Noi Vietnam; the ethics research committee Vietnam National Children’s Hospital, Ha Noi Vietnam; the Oxford tropical research ethics committee and the ethics research committee of the Ministry of Health, Vietnam.

Written consent is sought from parents/guardians, and assent from children who are developmentally appropriate and age-appropriate (as per local guidance) prior to trial participation. In the event a child is unable to give assent, for example, due to an altered conscious state, assent is deferred until recovery, and parental consent is used for enrolment. Opinions of children on their participation in the trial are taken on board at every opportunity, including assessments and follow-up visits. The rights of the child and/or their carer to refuse participation in the trial without giving a reason are respected, and withdrawal can occur at any stage of the trial. Re-consent is taken for children who turn 18 years of age during the trial (online supplemental material).

During the consent process, study objectives, the voluntary nature of participation and different treatments and possible toxicities by arm are explained to carers/participants using patient information sheets and reinforced during visits. An opt-in and opt-out option is provided on consent forms for participation in substudies, including a separate consent form for the diagnostics substudy (online supplemental material). The 6-month intensified ATT regimen has shown to be efficacious and safe but has never been subjected to a randomised comparison. Equipoise exists for aspirin/placebo in TBM given the lack of conclusive evidence from clinical trials to date (in adults or children). Previous concerns regarding the risks of developing the rare Reye syndrome in children have not stood up to recent scrutiny, nor has it been evident when using high doses in Kawasaki disease.

Safe CSF volumes are collected following published guidance.^44^ Total blood volumes and volumes required per study visit are considerably less than the blood volumes allowed for research in children internationally.^46^

Prior to the initiation of the trial at each clinical site, the protocol, all informed consent forms and carer/patient information materials are submitted to the appropriate ethics committee for approval. Further protocol amendments will also require ethical approval before implementation.

The principles of the UK General Data Protection Regulation are followed at all participating sites. Participants’ anonymity is maintained, and identities are protected from unauthorised parties. Clinical information will not be released without written permission, except as necessary for monitoring purposes. All consent forms and CRFs are stored in a secure filing cabinet at study sites. Only the PI and local investigators have access to the trial dataset solely for research purposes.

The SURE TSC is the custodian of the data and specimens generated from the SURE trial. All publications will be approved by the Trial Management Group (TMG) and TSC before submission for publication. Any publication arising before the end of the trial (not by randomised groups) will also be approved by the IDMC. In line with UCL policy, the results of publicly funded research will be freely available, and manuscripts arising from the trial will, wherever possible, be submitted to peer-reviewed journals, which enable Open Access via UK PubMed Central within 6 months of the official date of final publication. Dissemination of findings will also occur with patient and public involvement (PPI) and community advisory board input to communities, media, international TB conferences and key stakeholders, including the WHO Child and Adolescent TB Working Group. All conference presentations will be made available as soon as possible after the event via the MRCCTU and participating trial site websites.

### Study status

Enrolment in the SURE trial commenced in March 2021, and trial follow-up will be completed by the end of December 2025. Recruitment of 369 children was completed in June 2024, at which time loss to follow-up was low.

### Indemnity

Participants exit the trial at 72 weeks without post-trial care. UCL holds insurance against claims from participants for injury caused by their participation in the clinical trial. In addition, research facilities/clinics have a duty of care to the participant and hold clinical negligence insurance cover for harm caused during the trial.

### Trial governance and committees

A TMG comprising the Chief Investigator, lead site investigators and members of the MRCCTU and Oxford University Clinical Research Unit Clinical Trial Unit (OUCRU CTU) teams is responsible for the day-to-day management of the trial. The IDMC is the only group that sees confidential, accumulating data for the trial by the randomised arm and can recommend premature closure or reporting of the trial to the TSC.

The TSC has membership from the TMG plus independent members, including the Chair. The TSC provides overall supervision for the trial and advice. The ultimate decision for the continuation of the trial lies with the TSC. The frequency of meetings is dictated in the IDMC and TSC charters but has been around every 6 months to date.

A central (blinded) endpoint review committee (ERC) will ascertain the primary endpoint for TBM in control versus intervention arms for both randomisations 1 and 2. Additional endpoints to be reviewed will be:

All causes of death.Specific AEs, for example, DILI (grade 2 and above) and all SAEs.Prespecified secondary endpoints (online supplemental
table S6).

Furthermore, the ERC will determine if the event is related to the underlying TBM disease or to the treatment.

UCL is the sponsor of SURE and delegates to MRCCTU and OUCRU the responsibility of overseeing the implementation of the study by ensuring that arrangements are put into place for adequate management, monitoring, analysis and reporting of the trial.

UCL is the SURE trial sponsor (MRCCTU at UCL, [name]).

## Discussion

Interventional trials in paediatric TBM are few and challenging to conduct but are critically important for improving the treatment of TBM, which disproportionately kills or disables children. The SURE trial is the largest randomised paediatric TBM treatment trial to date and provides an opportunity to address several other important research questions. It is the first phase-3 trial to study both the role of a shortened intensive ATT regimen and anti-inflammatory therapy for childhood TBM using a factorial design. Children bear the heaviest burden of TBM, yet this vulnerable group, which stands to benefit the most from new treatment approaches, is often excluded from randomised clinical trials (RCTs). Much of the mortality and morbidity is driven by the host immuno-inflammatory response to *M. tuberculosis*. Treatment advancements to reduce mortality and neurological sequelae from TBM should, therefore, evaluate both new anti-inflammatory agents and optimised ATT regimens, where possible in the same trial.

In recent years, there has been a surge in adult TBM treatment clinical trials, which primarily aim to optimise treatment by intensifying the ATT regimen with high-dose rifampicin (up to 35 mg/kg), with or without linezolid as an alternative fourth agent.^48^ However, most active trials exclude children and even adolescents (table 1) and to date, there has been just one other paediatric TBM ATT treatment trial, TBM-KIDS. In this phase 2 open-label trial, children were randomised to high-dose rifampicin (30 mg/kg), with or without levofloxacin (instead of ethambutol) for 8 weeks, followed by 10 months of continuation phase versus standard of care.^22^ However, due to challenges with recruitment, this trial was halted after just 37 children were randomised. While treatment shortening to 6 months for drug-susceptible TBM has been the standard of care in the Western Cape of South Africa for more than 30 years, and has informed a recent conditional treatment recommendation by the WHO,^49^ there have been no published head-to-head clinical trials with the standard of care. Two active TBM treatment-shortening trials are in progress, of which SURE is the only paediatric one. The other, IMAGINE-TBM (Improved management with antimicrobial agents isoniazid rifampicin linezolid for TBM) adult trial is a phase 2/3 randomised open-label trial comparing a 6-month TBM treatment regimen of high-dose rifampicin (35 mg/kg), high-dose isoniazid (10–15 mg/kg), pyrazinamide (25 mg/kg) and linezolid (1200 mg) for 8 weeks followed by rifampicin (35 mg/kg) and isoniazid (10 mg/kg) for 16 weeks (total 24 weeks) to a 9-month standard-of-care regimen in adolescents and adults. Unlike our trial, IMAGINE-TBM does not include adjuvant anti-inflammatory as an additional intervention. The additional advantage of the SURE trial design is its broad generalisability. If shortened, intensified ATT is non-inferior to the current 12-month standard, we anticipate swift transfer into clinical practice via changes to WHO guidelines, which are followed in most low-middle income countries. If high-dose aspirin is shown to be superior and safe, an inexpensive and widely accessible treatment would then be rapidly implemented into guidelines. Thus, the SURE trial is uniquely placed to answer important research gaps in the neglected field of TBM and potentially provide new TBM treatment approaches to improve outcomes while significantly reducing the duration of treatment. Study limitations include the enrolment of children who may not truly have TBM, as microbiological evidence of *M. tuberculosis* in CSF was not mandated for enrolment in this pragmatic trial, and mortality rates may not be an accurate reflection of the real world due to close monitoring and follow-up within the trial context.
